## Abstract

**Background:**

Arthroscopic rotator cuff repair (ARCR) often causes unbearable postoperative pain, even more severe than before surgery. Opioids are the drugs of choice for temporary postoperative analgesia. However, this conventional approach also has some side effects and potential for drug abuse. The aims of this study are expected to verify the effect of 5% lidocaine patch (LP5) on the intensity of early postoperative pain, functional recovery and quality of life in patients undergoing ARCR.

**Methods:**

In this randomized, double-blind, and placebo-controlled clinical trial, a total of 102 postoperative patients undergoing ARCR will be randomly assigned to either the LP5 group, receiving topical lidocaine analgesia, or the placebo control group. The primary outcome measure will be the change in the American Shoulder Elbow Surgeons score from pre-operation to 90 days post-operation. Secondary outcomes will include pain scores, range of motion, opioid use, safety indicators, blinding assessment and several shoulder function score questionnaires. The effect of the allocated treatment will be assessed at preoperative baseline and at 7-, 14-, 30- and 90-day postoperatively.

**Discussion:**

In this study, the efficacy and safety of the 5% lidocaine patch will be evaluated in terms of short-term clinical symptoms in patients undergoing ARCR. The results of this study will help determine whether LP5 is effective in early functional recovery in ARCR and whether it relieves pain and reduces opioid consumption.

**Trial registration:**

Chinese Clinical Trial Registry (http://www.chictr.org.cn) ChiCTR2200060108. Registered on 19 May 2022.

## Background

Arthroscopic rotator cuff repair (ARCR) has been proven to provide excellent clinical outcomes, such as restoration of tendon integrity and improvement in daily living, in patients with symptomatic rotator cuff tears who have failed to respond to conservative treatment [1, 2]. Although the short and long-term clinical outcomes of ARCR are very promising, postoperative pain is strongly associated with early return of mobility and patient satisfaction, particularly in intense postoperative pain [3]. Numerous methods of postoperative pain management after ARCR have been practised clinically, including oral and intravenous medications, regional nerve block, intralesional anaesthesia, periarticular injections [4, 5] and multimodal anaesthesia [6]. Opioids were once the cornerstone of post-ARCR pain management, however, their significant side effects and high addictive potential cannot be ignored as well [7–9]. Interscalene brachial plexus block (IBPB) also has some disadvantages, such as short timeliness, technical difficulty and a high probability of recurrence of pain [10, 11].

Five per cent lidocaine patch (LP5) is the first-line recommendation for postherpetic neuralgia and may reduce opioid consumption in acute postoperative pain [12–14]. Lidocaine is a voltage-gated sodium channel blocker. The proposed mechanism of action is to block abnormally expressed sodium channels following nerve injury, and lidocaine reduces abnormal peripheral nerve discharge and decreases peripheral sensitivity, thus exerting a local analgesic effect [15, 16]. In addition, the effectiveness of the topical lidocaine patch for other conditions, such as low back and myofascial pain, osteoarthritis of the knee and perioperative pain has been confirmed by previous studies [17–21].

To identify whether the lidocaine patch could produce similar beneficial effects in post-arthroscopic analgesia, we conducted a prospective double-blind randomized trial in patients undergoing ARCR. We hypothesized that lidocaine patch treatment immediately after ARCR would result in clinically and statistically significant improvements in pain levels, functional recovery and the use of oral analgesics.

## Methods

### Trial design

The study will be a prospective, single-centre, randomized, placebo-controlled, double-blind, superiority trial in the First Affiliated Hospital of Soochow University conducted from May 2022 to December 2022, enrolling patients undergoing arthroscopic rotator cuff surgery and was registered in the Chinese Clinical Trial Registry (ChiCTR.org ID: ChiCTR2200060108). The study protocol has been approved by our institutional review board, and all subjects provided written informed consent. The flow chart of trial participation is given in Fig. 1.

**Fig. 1 Fig1:**
[figure not shown]
Study flow chart

### Recruitment and informed consent

This study will be conducted in the First Affiliated Hospital of Soochow University. Patients with rotator cuff tears requiring arthroscopic rotator cuff repair (ARCR) will be mobilized from our outpatient centre. After confirming the patient's eligibility for inclusion and completing a baseline level assessment, the investigator will give a detailed presentation of the study protocol and potential risks, etc., and answer all the questions raised by patients and their families. Each patient will sign an informed consent form. Upon enrolment, participants will be coded with a unique number.

### Eligibility

All patients confirmed with rotator cuff tear by MRI with symptoms (pain and/or weakness) and are failed to conservative treatments will be included. The exclusion criteria are (1) history of allergy to lidocaine or adhesive, (2) other significant organ disorders or substance abuse, (3) clear radiographic evidence of osteoarthritis of the glenohumeral joint, (4) presence of inflammatory arthritis including rheumatoid, (5) a history of ipsilateral shoulder dislocation or surgery, (6) irreparable tears, (7) pregnancy or heart disease, and (8) inability to understand questionnaires or express the level of pain.

### Withdrawal and termination criteria

Participants can withdraw from this trial in the following reasons:Deciding to withdraw by themselves at any time and for any reason.Loss to follow-up.Experiencing serious adverse events or allergic reaction.

### Randomization and blinding

Prior to the start of the study, randomization will be performed using a computer-generated table of random numbers by the research pharmacy not involved in the screening of subjects. Included participants will be randomly assigned with a 1:1 allocation to either the lidocaine or placebo group, with each patient having an equal probability of being assigned to either the experimental treatment group or the placebo group. The material, size and colour of the placebo patch will be similar to LP5 as far as possible. Patients will use the patches under the guidance of their surgeons. The group allocation protocols will be enclosed in opaque envelopes to ensure blinding of the investigators, patients, and data analysts. These envelopes will be sealed and could only be opened after the study is completed.

If a subject experiences a serious adverse event or requires emergency resuscitation during the trial, whether or not it is related to the intervention, the intervention received by the subject will be disclosed. Subjects who disclose the intervention will be considered as drop-out cases. If the intervention is disclosed for more than 20% of participants, the trial will not be considered double-blind.

In addition, the allocation scheme of the intervention will be confidential to the evaluators collecting outcome data throughout the study. The statistical analysts will also not know whether participants are in the LP5 or placebo group until the statistical analysis is completed.

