### Intervention

The group allocation protocol will be performed prior to the procedure. Based on the random number, a pre-prepared opaque envelope containing either 5% LP measuring 14 × 10 cm^2^ and containing 700 mg of lidocaine or placebo patches was allocated to the patient. There is no difference between the placebo patches and LP5 patch in appearance or structure, but the placebo does not contain lidocaine. The patch will be divided into strips and applied around the shoulder crest immediately after surgery. The patch will be replaced with a new one every 12 h until 2 weeks postoperatively. Patients, test site medical staff and investigators were blinded to group allocation. In cases of severe shoulder pain, painkillers will be allowed as emergency medication and should be documented in the medical record. Patients will also be asked to record the name, dose, date, frequency and exact time of medication used and to report to the researcher if they have taken any medication during the study. Patient compliance will be maintained and monitored through good communication and constant reminders between medical staff and patients. Although patients will be advised to adhere to the protocol, it is not possible to fully exclude those patients who independently decide to undergo and not report other treatments or measures. We will explain in detail to the patients and their family members simultaneously. A close follow-up and telemedicine will be performed during the trial.

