### Adverse event management

Any adverse events (AEs) occurring to participants during the clinical trial, whether or not they are related to the intervention, will be assessed and recorded at any time. Adverse events will be recorded on a designated Clinical Case Observation Form (CRF) Adverse Event Form and classified according to the Medical Dictionary of Regulatory Activities (MedDRA). During this period, if the participant feels a slight burning, tingling, redness, blistering or breakage of the local skin, the area will be disinfected and covered with sterile gauze to prevent infection. Other side effects caused by lidocaine such as: hypotension, dizziness, slowed heart rate and gastrointestinal reactions will be recorded on the CRF. Drug safety will be assessed by blood routine examination (BRE), urine routine test (URT), liver function tests (LFTs) and other indicators of significant organ damage. Indicators of joint cavity infection such as erythrocyte sedimentation rate (ESR), anti-streptococcus hemolysinv (ASO) and rheumatoid factor (RF) will be recorded. Data will be collected on complications and adverse reactions, including death, reinfection, reoperation, medical complications, rash or allergic reactions. Serious adverse events (SAEs) will have to be reported to the Ethics Committee of the First Affiliated Hospital of Soochow University within 24 h. In the event of a medical emergency, random coding and group allocation of individuals can be determined through standard operating procedures. These complications will be included in the secondary outcome of this study.

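### The code-break statements conflict, and the mandatory one unblinds and drops participants for unrelated events up to day 90, long after the last patch

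*Protocol article*

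**What the plan says.** Three statements in two sections of the protocol article govern when an individual allocation may be revealed.

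- *Randomization and blinding*, first paragraph, on the allocation envelopes: "These envelopes will be sealed and could only be opened after the study is completed". No exception is attached.
- *Randomization and blinding*, second paragraph: "If a subject experiences a serious adverse event or requires emergency resuscitation during the trial", then, "whether or not it is related to the intervention, the intervention received by the subject will be disclosed". Two consequences follow. For the participant: "Subjects who disclose the intervention will be considered as drop-out cases", which in context must mean those whose allocation has been revealed. For the trial: "If the intervention is disclosed for more than 20% of participants, the trial will not be considered double-blind".
- *Adverse event management*: "In the event of a medical emergency, random coding and group allocation of individuals can be determined through standard operating procedures".

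The third paragraph of *Randomization and blinding* protects the outcome evaluators: "the allocation scheme of the intervention will be confidential to the evaluators collecting outcome data throughout the study". It also keeps the analysts blind until the analysis is finished. None of these sentences says who receives a disclosed allocation.

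On timing, *Intervention* says: "The patch will be replaced with a new one every 12 h until 2 weeks postoperatively". Follow-up runs to day 90, when the primary outcome, change in ASES from baseline, is measured.

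**The concern.** A site reading these sections cannot tell which rule applies. The envelope sentence forbids opening before the study ends, the next paragraph orders disclosure, and the adverse event section permits it. For an emergency the practical answer can be guessed. For an SAE that is not an emergency it cannot: one section makes disclosure compulsory and the other does not provide for it.

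The compulsory rule is also broad. It ignores relatedness, and its only time limit is that the event occurs during the trial. An unrelated SAE on day 60 would trigger disclosure 46 days after the last patch (60 − 14 = 46). The article gives no reason why the allocation would be needed then.

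At stake are the blind of a placebo-controlled trial and the completeness of its primary outcome. Each disclosure makes the participant a drop-out. If follow-up then stops, the day-90 ASES is lost. If follow-up continues and the participant has been told the arm, patient-reported outcomes are open to bias.

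**Working it through.** The plan states no figure on this point, so the check is a comparison of texts followed by simple arithmetic on scope.

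**The statements side by side**

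| Statement | Trigger | Force | Time limit |
|---|---|---|---|
| A. Envelope sentence | None | Forbids opening | Until study completion |
| B. Disclosure paragraph | Any SAE or emergency resuscitation, related or not | Mandatory | Any time in the trial |
| C. Adverse event section | Medical emergency | Permissive, through standard operating procedures | None stated |

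- A against B and A against C: taken literally, each pair conflicts, because A allows no opening before completion.
- B against C: they overlap in emergencies, where C can serve as the procedure for carrying out B. They part on an SAE that is not a medical emergency, which B requires to be disclosed and C does not cover. They also differ in force.

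**How much of B's window lies after treatment**

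Inputs: last patch at 2 weeks, day 14 (*Intervention*); end of follow-up at day 90 (*Outcomes measurement* and Table 1).

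- Days after the last patch: 90 − 14 = 76.
- Share of follow-up: 76 / 90 = 0.844, or 84%.

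This is a share of calendar time, not of events.

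**How many participants B would reach**

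Inputs: 102 participants (*Sample size calculation*); SAE rate assumed, because the documents give none. Expected disclosures = 102 × rate. If events were spread evenly over follow-up (a second assumption), the number after the last patch is that product × 76/90.

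| Assumed SAE rate | Expected disclosures | Of these, after the last patch (even spread) |
|---|---|---|
| 2% | 102 × 0.02 = 2.0 | 1.7 |
| 5% | 102 × 0.05 = 5.1 | 4.3 |
| 10% | 102 × 0.10 = 10.2 | 8.6 |

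If SAEs cluster soon after surgery, the last column is too high. The middle column counts all SAEs, including those for which the allocation is truly needed, so it is a ceiling on needless disclosures.

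**What each disclosure costs**

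The plan needs 41 per group, 82 in all, and recruits 102, so the drop-out allowance is 102 − 82 = 20 participants. At a 5% SAE rate, about 5 of those 20 would be classed as drop-outs by the disclosure rule alone. Some might have left anyway, since the withdrawal criteria already list SAEs as a reason.

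**The case against.** The strongest reply is that *Randomization and blinding* reads naturally as a general rule followed at once by its exception, with the adverse event section supplying the mechanism. The envelopes might also be the master allocation, with a separate route for single code breaks. Both readings are sensible, and a site would probably act on one of them. But the text states neither, and neither removes the difference in trigger and force between the disclosure paragraph and the adverse event section. It would go too far to infer that all three statements exclude one another: the second and third can both be obeyed in an emergency.

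A reader might also infer that the rule biases the primary outcome through self-report. The documents do not establish that. Disclosed participants become drop-outs, so a later ASES may never be collected. Bias arises only if the participant is told the arm and is still assessed, and the article settles neither point. Nor does the section on functional questionnaires name ASES in its list of patient-reported instruments; it mentions the score later in the same paragraph. Evaluators and analysts are already kept blind by an explicit statement.

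A third tempting inference is that these disclosures endanger the trial's claim to be double-blind. The limit is more than 20%, and 0.20 × 102 = 20.4, so 21 disclosures would be needed. With a binomial count, the chance of 21 or more is about 0.00000003 at a 5% SAE rate and about 0.001 at 10%. That argument does not stand.

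Finally, custody of the code, hours of access and request logs belong in the standard operating procedures that the article mentions. Their absence from a condensed article is not a fault. Disclosing after every SAE may also be meant as caution, but the article gives no reason for extending it to unrelated, non-emergency events after the last patch.

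**Conclusion.** The concern holds in a limited form. The envelope sentence conflicts, as written, with the two statements that allow or require a code break. Those two overlap but differ in trigger and force. The mandatory version reveals the allocation for unrelated, non-emergency SAEs through to day 90, 76 days beyond the last patch, and makes each such participant a drop-out. That is an avoidable loss of blinding. It also brings either avoidable loss of day-90 ASES data or, if the participant is told and still assessed, a risk of bias in patient-reported outcomes.

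The size is probably small: about 2 to 10 of 102 participants at assumed SAE rates of 2% to 10%, only some of them needlessly disclosed. The textual conflict does not depend on these assumptions; the count depends on them entirely. The judgement that some disclosures are needless rests on the article giving no use for the allocation in such events.

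**What to change.** Replace the three statements with one code-break rule, stated once and cross-referenced between *Randomization and blinding* and *Adverse event management*:

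1. Add to the envelope sentence an explicit exception for individual code breaks.
2. Tie disclosure to a need for the allocation, under the procedure already named in *Adverse event management*, and not to the SAE label alone. Which clinical situations create that need is for the trial's clinicians and ethics committee to settle; the point here is that the two sections must give the same answer.
3. Limit disclosure to those who need the allocation, so that the participant, where possible, and the evaluators and analysts in every case, stay blind.

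The cost is protocol wording, submitted to the ethics committee and the registry as the article's own amendment section provides. It needs no extra participants or visits and no change to the analysis. Custody and logging can stay in the standard operating procedures.

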### Statistical analysis

The final data will be entered and counted by a professional statistician using SPSS 26.0 (IBM, Armonk, NY, USA). For continuous variables, the normality of measured data distributions will be evaluated using the Shapiro-Wilk test. Measurements will be expressed as mean ± standard deviation, if the data are normally distributed with uniform variance. Paired *t*-tests will be used for within-group comparisons before and after treatment, and independent samples *t*-tests will be used for between-group comparisons before and after treatment. If the data do not conform to a normal distribution or have an uneven variance, the measurement data will be expressed as median (interquartile range) [M(Q)] and the Wilcoxon rank sum test will be used for the analysis of the data before and after treatment. For categorical variables, chi-square tests or Fisher’s exact tests will be used to examine differences between groups and to describe effect sizes in terms of percentages and frequencies. Prior to any analysis, the pattern and reasons for missing data patterns will be investigated. The primary analysis will be conducted as an intention-to-treat analysis, which includes all participants with missing outcome data, unless there is clear evidence that its underlying assumption is inappropriate. Multivariable imputation by chained equations method will be used to impute missing data for the sensitivity analysis for the primary and secondary outcomes. *P*<0.05 indicates that the threshold of statistical significance has been reached.

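### Classing participants unblinded after a serious adverse event as drop-outs is not reconciled with the intention-to-treat primary analysis or with 3-month follow-up of all patients

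*Protocol article*

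**What the plan says.** Four sections of the protocol article bear on this point.

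- **Randomization and blinding.** The trigger is a serious adverse event or a need for emergency resuscitation, and "whether or not it is related to the intervention, the intervention received by the subject will be disclosed". The consequence is fixed in the next sentence: "Subjects who disclose the intervention will be considered as drop-out cases". A separate rule says the trial no longer counts as double-blind once disclosure exceeds 20% of participants.
- **Withdrawal and termination criteria.** Among the reasons for which participants can withdraw from the trial is "Experiencing serious adverse events or allergic reaction". Stopping the patch and leaving follow-up are not distinguished.
- **Statistical analysis.** "The primary analysis will be conducted as an intention-to-treat analysis, which includes all participants with missing outcome data", with the exception "unless there is clear evidence that its underlying assumption is inappropriate". For approximately normal data, "independent samples *t*-tests will be used for between-group comparisons before and after treatment"; otherwise a rank-sum test is used. On missing values: "Multivariable imputation by chained equations method will be used to impute missing data for the sensitivity analysis for the primary and secondary outcomes".
- **Data collection and management.** Every patient is to be followed for 3 months. Reinfection and reoperation are among the complications recorded, and Adverse event management makes complications a secondary outcome.

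The article does not define a drop-out case.

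**The concern.** Intention-to-treat keeps each randomised participant in the assigned arm whatever happens afterwards. The disclosure rule changes a participant's status because of something that happened after randomisation, and it does so automatically: the participant need not have refused further visits.

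If drop-out status means that the 90-day ASES is not collected or not used, the primary comparison loses a selected group. Two features make the selection potentially informative. First, a reoperation or infection after shoulder surgery could plausibly lower shoulder function, which ASES measures. Second, the patches are said to differ only in lidocaine, so a systemic lidocaine effect serious enough to trigger disclosure could arise in one arm only. Removing poorly recovering participants raises the mean of those who remain, which flatters whichever arm loses more of them.

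**Working it through.** **Step 1: what drop-out status implies for the primary test.**

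- Sample size calculation sets 41 per group, allows 20% drop-out and recruits 51 per group. 41 / (1 − 0.20) = 51.25, and 51 × 0.80 = 40.8, or about 41. In that section, then, drop-outs are participants who do not count towards the 41.
- The stated between-group tests (t-test or rank-sum) need an observed value for each participant.
- Chained-equation imputation is assigned to the sensitivity analysis, and no imputation is named for the primary analysis.
- It follows that a participant handled as a drop-out, with no 90-day ASES used, contributes nothing to the primary comparison, even if still listed in the intention-to-treat set.

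**Step 2: the planned effect.** The pre-trial 3-month ASES scores are 74.94 (intervention) and 63.56 (control): 74.94 − 63.56 = 11.38 points.

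The 41 per group does not reproduce from these inputs. The root-mean-square of the SDs 15.56 and 18.42 is 17.05, and 2 × [17.05 × (1.960 + 1.282) / 11.38]² ≈ 47.2, hence 48 per group. That is a separate matter and does not affect this point.

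**Step 3: size of the bias.** Let q be the share of an arm removed and L the amount by which the removed participants' ASES change falls short of that of the participants who remain. If the remaining participants have mean m, the whole arm has mean (1 − q)m + q(m − L) = m − qL. Analysing only the remaining participants therefore overstates the arm mean by qL. With the same L in both arms, the bias in the difference is (q₁ − q₀) × L.

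The documents give neither q nor L. The values below are assumptions.

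| Removed, one arm | Removed, other arm | Bias, L = 10 | Bias, L = 20 |
|---|---|---|---|
| 2% | 2% | 0 | 0 |
| 5% | 2% | 0.03 × 10 = 0.3 | 0.03 × 20 = 0.6 |
| 10% | 5% | 0.05 × 10 = 0.5 | 0.05 × 20 = 1.0 |
| 10% | 2% | 0.08 × 10 = 0.8 | 0.08 × 20 = 1.6 |

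Against the planned effect, 0.3 / 11.38 = 2.6% and 1.6 / 11.38 = 14.1%. With 51 per arm, 2% is about 1 participant, 5% about 2.6 and 10% about 5.1.

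**The case against.** The strongest defence is that the text never removes anyone from the analysis set. The term for disclosed participants is undefined, and the intention-to-treat sentence expressly includes those with missing outcome data. A drop-out can be read as a missing value inside the intention-to-treat set. The article is also a condensed one, and a fuller protocol or SAP may define the term.

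Much of this stands. A reader might infer that the protocol prescribes an exclusion in outright contradiction of intention-to-treat, or that these participants certainly lose their 90-day ASES. The documents do not say either: withdrawal is permissive and all patients are to be followed for 3 months. What does not stand is that the missing-data reading solves the problem, because the only stated imputation is in the sensitivity analysis. Nor is this merely omitted detail: the article states a rule, and the rule sits badly with its own primary analysis.

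Three other stronger inferences also fail.

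- **Allergic reactions as a disclosure route.** They appear only as a withdrawal reason. Minor skin reactions receive local care, with no mention of disclosure, and known allergy to lidocaine or adhesive is an exclusion criterion. Differential loss by arm is possible but not shown.
- **A bias of 2–4 points.** This takes the 20% disclosure threshold as the share removed from one arm (0.20 × 10 = 2; 0.20 × 20 = 4). The threshold applies to all participants and governs only whether the trial is called double-blind. It is not an expected event rate, and the protocol describes safety concerns as minimal.
- **Using up the drop-out allowance.** Absorbing drop-outs is what the allowance is for, so this is not a defect in itself.

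**Conclusion.** The concern holds in a limited form. The disclosure rule, the withdrawal list, the intention-to-treat statement and the 3-month follow-up of all patients are not reconciled. Followed as written, participants handled as drop-outs after disclosure would not contribute to the primary comparison of 90-day ASES change.

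The likely size is modest: about 0.3–1.6 points, or 3–14% of the planned 11.38, if 5–10% are removed in one arm against 2% in the other and their ASES change is 10–20 points worse. With equal rates and deficits in the two arms the bias is zero, and if serious events are rare it will be small. All these rates and deficits are assumptions. The correction is still worth making before the data are unblinded, because a 90-day score that was not collected cannot be recovered.

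**What to change.** In Randomization and blinding, replace the drop-out sentence with wording such as: *Participants whose allocation is disclosed remain in follow-up to day 90 unless they withdraw consent, and are analysed in their randomised group. Each disclosure is recorded with its date and reason. A sensitivity analysis excludes disclosed participants.*

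In Withdrawal and termination criteria, list stopping the patch separately from withdrawing from follow-up, so that the first does not imply the second. In Statistical analysis, state how the primary comparison treats a 90-day ASES that is still missing.

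None of this changes when allocation is disclosed or when the patch is stopped.

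The cost is protocol wording and a little more follow-up effort, since the 30- and 90-day ASES visits already exist. Some outcomes will be assessed after unblinding, which is a real drawback for a patient-reported score. The sensitivity analysis without disclosed participants addresses it.

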### Data collection and management

After meeting all inclusion criteria and agreeing to participate, participants will be coded with a study number and all data referring to the patient will be recorded by this number rather than by name. Patients undergo routine preoperative laboratory and imaging assessments, including a review of preoperative medication and documentation of preoperative opioid use. A Case Report Form (CRF) will be used to collect information from participants, including baseline information, imaging results and follow-up visits. Shoulder mobility, clinical and demographic data, pain scores, and shoulder mobility scores will be collected at follow-up points. Data will also be collected on complications and adverse reactions, including death, reinfection, reoperation, medical complications, rash or allergic reactions. Independent researchers will manually enter the raw data storage. A Data Security Monitoring Board (DSMB) has been set up to review the reliability and security of the data. CRF as well as uploaded data will be stored in a secure cabinet or password-protected folder respectively. Access to study data by other researchers will be restricted. No interim analysis is planned for topical application of 5% lidocaine as the safety concerns are minimal unless required by the Steering Committee or DSMB because of safety concerns.

Acute pain after ARCR is a concern for patients. In addition, a close follow-up and telemedicine will be performed to reduce the rate of loss to follow-up. All patients will be followed up for 3 months for postoperative recovery and monitoring of complications. Patients will receive a text message or email two days before each postoperative follow-up point.

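### Participants unblinded after a serious adverse event are classed as drop-outs, which conflicts with the intention-to-treat primary analysis and the 3-month follow-up of all patients

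*Protocol article*

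**What the plan says.** Under Randomization and blinding, the article sets a trigger for disclosing the allocation: "If a subject experiences a serious adverse event or requires emergency resuscitation during the trial, whether or not it is related to the intervention". The trigger applies to both arms. The consequence follows at once: "Subjects who disclose the intervention will be considered as drop-out cases". I read this as covering anyone whose allocation is disclosed under that trigger.

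Two other sections bear on the same patients. Statistical analysis states: "The primary analysis will be conducted as an intention-to-treat analysis, which includes all participants with missing outcome data". Data collection and management states: "All patients will be followed up for 3 months for postoperative recovery and monitoring of complications". Neither makes an exception for unblinded patients. Chained-equation imputation is planned, but for the sensitivity analysis.

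Sample size calculation derives 41 per group, allows for 20% drop-out and recruits 51 per group. The primary outcome is the change in ASES from baseline to day 90.

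**The concern.** The rule lets something that happens after randomisation decide whether a patient's primary outcome counts. An intention-to-treat comparison is meant to prevent this: patients are followed and analysed as randomised, whatever happens to them later.

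The patch is worn for 2 weeks and the primary outcome is read at day 90. A serious adverse event in week 6 interrupts no treatment, yet it would still make the patient a drop-out.

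The losses need not be random. The article lists reinfection and reoperation among the complications to be collected. If such events are classed as serious (an assumption, since the article does not define the term), the patients lost would tend to be those with poorer shoulders. Imputation in a sensitivity analysis does not replace a score that the scheduled visit would have given, and a score not collected cannot be recovered later.

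**Working it through.** **1. What drop-out means in this article.** Sample size calculation needs 41 per group and recruits 51 to cover drop-outs. 102 − 2 × 41 = 20 patients are budgeted not to contribute, so there a drop-out is someone without a primary outcome.

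**2. The sections side by side.** Take a patient who has a serious adverse event, is unblinded, and can attend on day 90.
- Randomization and blinding: a drop-out, so on the meaning in step 1 no primary outcome.
- Data collection and management: followed for 3 months like everyone else, so the score is obtained.
- Statistical analysis: analysed by intention to treat, so an obtained score should be used.

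The first cannot hold together with the other two. Nothing in the article says that unblinded patients stay in follow-up or that their day-90 ASES is used.

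**3. The plan's own figure.** Inputs from Sample size calculation: 63.56 ± 15.56 (control) and 74.94 ± 18.42 (intervention), difference 74.94 − 63.56 = 11.38, two-sided α = 0.05, power 90%. With both SDs (root mean square 17.05) I get 48 per group by the normal formula and 49 by the t-test, not 41. The figure 41 is reproduced by a t-test with the control SD of 15.56 in both arms. This is a separate matter and does not affect the present point.

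**4. Precision lost.** I use the pilot SDs of the 3-month scores as a stand-in for the SDs of the change, which the article does not give.

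SE = √((18.42² + 15.56²)/n) = √(581.41/n). Power is from the noncentral t distribution, with equal losses per arm from 51.

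| Lost per arm | n per arm | SE | Power |
|---|---|---|---|
| 0 | 51 | 3.38 | 91.6% |
| 1 | 50 | 3.41 | 91.1% |
| 2 | 49 | 3.44 | 90.5% |
| 3 | 48 | 3.48 | 89.9% |
| 5 | 46 | 3.56 | 88.6% |

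These losses would come on top of ordinary drop-out.

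**5. Possible bias.** Suppose only observed scores are compared, and the lost patients would have scored D points lower than those retained. Then

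bias = (lost on LP5 − lost on placebo)/51 × D.

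D is not in the documents. For illustration I set it equal to the pilot difference, 11.38.
- Equal losses: 0.
- Net 1 patient: 1/51 × 11.38 = 0.22 points (0.07 SE).
- Net 2: 0.45 points (0.13 SE).
- Net 3: 0.67 points (0.20 SE).

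The sign depends on which arm loses more: more losses on LP5 flatter the patch, and more on placebo count against it.

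**The case against.** The best defence is that drop-out is only a status label. It stands just before a sentence that counts disclosures: "If the intervention is disclosed for more than 20% of participants, the trial will not be considered double-blind". The article never says that follow-up stops or that the patient leaves the analysis set, and how a status maps to analysis sets may be set out in the full protocol or the SAP, which are not shown. This stands in part. A reader might infer that the article excludes unblinded patients from the intention-to-treat set, but it does not say so, and patients with missing outcomes nominally remain in that set. The label reading is possible, yet nothing in the article supports it, and the one place that gives drop-out a working meaning points the other way. Site staff could reasonably stop follow-up.

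A second defence is that the rule has a blinding purpose, and this stands. A reader might infer that the rule is unnecessary because "the allocation scheme of the intervention will be confidential to the evaluators collecting outcome data throughout the study". That goes too far. Under Functional questionnaire assessment, ASES is handled with the patient-reported questionnaires, so a patient who knows the allocation may answer differently however well the evaluator is blinded. There is a real trade-off between blinding and completeness.

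Third, the expected effect is small. This also stands, as the figures show.

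Two further readings are tempting and not supported. One sets the 20% disclosure threshold against the 20% drop-out allowance, as if the plan accepted losing 20 of 102 patients to unblinding. The first figure decides only whether the trial is called double-blind; the two are unrelated. The other counts two more passages as errors. The withdrawal criterion "Experiencing serious adverse events or allergic reaction" is permissive: it lists when participants can withdraw. The statement "In the event of a medical emergency, random coding and group allocation of individuals can be determined through standard operating procedures" describes a mechanism and contradicts nothing.

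**Conclusion.** The point holds. As written, the rule turns obtainable day-90 ASES scores into missing data because of a post-randomisation event, against the article's own intention-to-treat analysis and its follow-up of all patients. This rests on reading drop-out as the sample size section uses it.

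The effect is probably small. No serious adverse event rate is given, so neither the number affected nor the direction of bias can be determined. A reader might infer that the rule favours LP5; the documents do not support that, since the trigger covers both arms and equal losses give no bias. The sizes shown (power of 89.9% or more with up to 3 lost per arm, bias up to 0.7 points for a net imbalance of 3) rest on the pilot SDs and an assumed deficit of 11.38 points. The sentence should be corrected because the change is cheap and uncollected scores cannot be recovered.

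**What to change.** In Randomization and blinding, replace the drop-out sentence with: *Participants whose allocation is disclosed remain in follow-up and in the intention-to-treat analysis, flagged as unblinded.* Keep the outcome evaluator blinded, and add a sensitivity analysis of the primary outcome that examines the flagged patients.

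The cost is one sentence, one flag on the case report form and one sensitivity analysis. No visits or patients are added, because the day-30 and day-90 assessments are already scheduled. The downside is that a few patients may complete the questionnaires knowing their allocation, which is why the flag and the sensitivity analysis are needed.
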